### Control: waitlist control group

Participants allocated to the WLC group will be informed that they will be able to access the treatment after a waiting period of 6 weeks, during which they will complete three sets of online questionnaires. WLC participants will be sent automated emails via the REDCap platform with a link to complete questionnaires the day after their interview is completed (baseline, T1), 2 weeks later (T2), and 6 weeks post-baseline (T3). At T3, they will also be contacted to re-complete the telephone diagnostic interview, after which they will schedule the start date for their treatment week if they still choose to participate. WLC participants will follow the same procedure as the treatment group before (preparation call), and during their treatment week, receiving the treatment and clinician support over 1 week, and complete post-treatment questionnaires 1 week after completing their intervention. This post-treatment assessment will be used to assess WLC participants’ immediate treatment outcomes which will be included in the analysis of predictors of treatment outcome. The WLC will not be asked to complete any further follow-up assessments to minimise participant burden.

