Despite these encouraging initial findings, further investigation is needed to evaluate the program’s efficacy. Because of the lack of control group in the pilot trial, it is unknown whether the improvements observed were attributable to the treatment or to another factor, such as the passage of time or repeated assessments. Further, the study relied on self-report measures of social anxiety. The lack of follow-up assessment also means it is unknown whether the gains observed were maintained over the longer term. A RCT with a larger sample, comparison to a control group, and inclusion of follow-up and clinician-rated assessment is now needed to evaluate the efficacy of the program.

A further important area of investigation is for whom intensive iCBT is best suited. While an intensive online format has potential for rapid symptom improvement, unwanted side effects (e.g. feeling overwhelmed from time pressure) have been reported by some participants in intensive iCBT (e.g. [20, 21, 33]), so better understanding of which patients may benefit most from this new treatment format is important. One study [46] of standard-paced iCBT for SAD for example found that older age and female gender predicted better treatment adherence and outcome, while another [47] found lower baseline severity predicted better post-treatment outcomes. A meta-analysis of 28 studies of standard-paced CBT for SAD however found no consistent evidence for strong pre-treatment predictors of response across the studies [48]. It is also unclear whether the efficacy of intensive iCBT is impacted by common comorbidities in SAD, such as depressive symptoms and personality pathology, which have been shown to predict poorer treatment response in standard-paced CBT [48, 49]. We therefore sought to investigate these questions further by examining predictors of treatment response and adherence to intensive iCBT for SAD, including demographic characteristics (age, gender) and comorbid psychopathology (baseline severity of depression and SAD symptoms, personality pathology).

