### The current study

The proposed research will examine whether delivering iCBT in an intensive format over 1 week is effective in treating SAD symptoms relative to a waitlist control (WLC) group. A WLC condition was chosen as a comparator for several reasons. First, it provided a practical and feasible first step in evaluating the efficacy of this treatment, to determine whether a larger, more costly trial to compare it to an active treatment group or standard-paced CBT is warranted. WLC provided a clearer measure of treatment effects as it is more standardised than a usual care control group. Usual care control groups introduce more heterogeneity because participants receive varying levels and types of treatment. The WLC design also controlled for some factors such as the passage of time, the effects of repeated assessment, and regression to the mean which may have explained some improvements observed in the previous pilot trial. This study is the first RCT evaluating the efficacy of intensive, individual, online CBT for SAD. It is strengthened by the addition of follow-up assessment 1 month post-treatment and a clinician-rated diagnostic interview to assess the efficacy of the treatment beyond the self-report measures used in the pilot trial.

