### Trial aims and hypotheses

This protocol has been reported according to SPIRIT guidelines for reporting of trial protocols [50, 51]. The primary aim of this study is to investigate the efficacy of the intensive iCBT for SAD program [44] in improving symptoms of social anxiety at post-treatment and 6-week follow-up, relative to a WLC group. The secondary objectives of the trial are to evaluate the efficacy of the program in reducing symptoms of depression and functional impairment/quality of life at post-treatment and follow-up. A third aim is to further explore the program’s acceptability and feasibility. We aimed to test whether the strong adherence and satisfaction observed in the pilot trial were replicated in a larger sample and outside of the COVID-19 pandemic context. A fourth aim is to explore predictors of treatment effectiveness, including participant age, gender, baseline symptom severity, and personality.

The primary hypothesis is that participants who receive the intensive iCBT for SAD intervention will show significantly reduced social anxiety symptom severity compared to the WLC group. We also hypothesise that intensive iCBT for SAD will be significantly more effective at improving participants’ comorbid depressive symptoms and increasing quality of life relative to the WLC group. The third hypothesis being tested is that intensive iCBT for SAD will be acceptable to participants according to high adherence (> 80%) and treatment satisfaction ratings. A further set of exploratory analyses will investigate whether the effectiveness of the intervention is predicted by participant age, baseline symptom severity, and personality functioning.

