### Eligibility criteria

Inclusion criteria includes adults aged 18 years or over, residing in Australia, fluency in written and spoken English, access to a computer and the internet, elevated scores on both the Social Interaction Anxiety Scale [> 34; SIAS, [52]] and the Social Phobia Scale [> 24; SPS, [52]], meeting DSM-5 diagnostic criteria for SAD according to a telephone diagnostic interview, willingness to provide basic demographic information and their general practitioner’s (GP) contact details, and on a stable dose of medications if applicable (no new medications or changes to existing medications in the 2 months prior to applying for the study).

Exclusion criteria are as follows: self-disclosed pre-existing diagnosis of schizophrenia, psychosis or bipolar disorder, daily or nearly daily suicidal ideation (score of ‘3’ on item 9 of the Patient Health Questionnaire-9 [PHQ-9; [53]]), or recent suicidality as determined by clinician interview (i.e. current suicidal intent, self-harm, or suicide attempts in the past 5 years), very severe depression (PHQ-9 scores of ‘24’ or above), currently receiving CBT, or commenced or changed mental health medication in the 2 months prior to application.

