### Statistical analysis

All analyses will be undertaken using intention-to-treat approach. Linear mixed models, with a random intercept for subject will be used to analyse primary and secondary outcomes, and covariances matrixes used to assess relationships between variables. This approach will be used to manage missing data and account for correlation between repeated measures. Before conducting the analyses, patterns of missing data will be assessed through data visualisation, and Little’s Missing Completely at Random (MCAR) test to determine whether the data are missing at random. If there are significant group differences (as determined by independent samples *t*-tests) in the amount of time elapsed between the intake interview and completion of baseline measures, this variable will be included as a covariate in the linear mixed models. Planned contrasts will be used to compare pre- and post-treatment, and pre-treatment and 1-month follow-up, and planned pairwise comparisons will be used to compare between-groups at post-treatment and follow-up. To control for the risk of type 1 error with a co-primary outcome, the alpha level for significance will be adjusted using a Bonferroni correction (alpha set at 0.025 to determine statistical significance for the SIAS and SPS co-primary outcome measures). Linear mixed models will be utilised to test the predictors of treatment outcome. Within- and between-group effect sizes will be calculated using Hedges’ *g* (with 95% confidence intervals) to estimate the within-group changes from baseline to post-treatment, and baseline to follow-up, and between-group differences on primary and secondary outcome measures at post-treatment and follow-up.

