### Limitations of the study and future research

The results of this study should be interpreted with consideration of some limitations. Firstly, the use of a passive (waitlist) versus active control group means that while it is discouraged for participants to commence other therapies or medication during the waiting period, we are unable to control for other care they receive during this time. Future studies would benefit from comparing the treatment to an active control condition such as a digital placebo program or a psychoeducation control group. Future research should also compare this intervention to standard-paced iCBT or intensive face-to-face CBT. While our predictor analyses will provide some initial understanding as to whom this intensive approach is most suited, a RCT comparing the intensive and standard-paced formats (and to traditional face-to-face formats) will provide further clarification as to who benefits most from these diverse treatment approaches. A further limitation relates to the relatively short follow-up period; future studies would be strengthened by a longer-term follow-up period (e.g. 3 months or longer) to measure the longer-term impact of the intervention. In addition, our power calculations have been informed by meta-analyses of standard paced iCBT [92] and may have overestimated the expected between-group effect size. Future studies should consider using minimal important clinical differences to inform sample size calculations, to ensure similar studies are powered to detect changes that are not only statistically significant, but clinically meaningful.

Second, the risk of bias cannot be completely eliminated in the collection of some study data. It is not feasible to blind researchers to participant group allocation follow-up interviews. We will also rely on participant self-report to measure some engagement variables (length of time spent reading module material or practising skills) so this may be inaccurate. Relatedly, as the treatment is completed by participants online rather than in vivo with a clinician, it is not possible for clinicians to model the therapy skills (e.g. exposure). As such, it will be unclear if participants are implementing these skills with complete fidelity to the program instructions.

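### The predictor analysis includes waitlist participants' uncontrolled outcomes after delayed treatment, so it can identify prognostic factors but not, as the aim is worded, for whom the programme works

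*Protocol article*

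**What the plan says.** The question is set in the Background, section 7-day iCBT for social anxiety disorder: "A further important area of investigation is for whom intensive iCBT is best suited". Trial aims and hypotheses turns it into an objective: "A fourth aim is to explore predictors of treatment effectiveness, including participant age, gender, baseline symptom severity, and personality". The same section gives its status: "A further set of exploratory analyses will investigate whether the effectiveness of the intervention is predicted by participant age, baseline symptom severity, and personality functioning".

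Two places describe the analysis. Control: waitlist control group says that the post-treatment assessment of waitlist participants captures their "immediate treatment outcomes which will be included in the analysis of predictors of treatment outcome". Statistical analysis adds only: "Linear mixed models will be utilised to test the predictors of treatment outcome". No group-by-predictor term is named.

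The current study justifies the waitlist partly because it controls for elapsed time and for "the effects of repeated assessment, and regression to the mean which may have explained some improvements observed in the previous pilot trial". Limitations of the study and future research says that the predictor analyses "will provide some initial understanding as to whom this intensive approach is most suited", and calls for a trial against standard-paced and face-to-face formats to clarify the matter. It does not list the lack of a control in the predictor data as a limitation.

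**The concern.** Whom a treatment suits is a question of effect modification: does the difference between treated and untreated vary with the predictor? Scores from waitlist participants after they cross to treatment have no concurrent comparator, so they can inform only a before-and-after description of treated people. A characteristic that predicts a good score there may predict an equally good course without treatment.

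Baseline severity is the most exposed of the named predictors, because measurement error in the baseline score also enters the change score. Severe cases then appear to improve more even when everyone benefits equally. For age and gender there is no such built-in correlation, and the difficulty is only prognosis versus effect modification. For depression and personality scores, regression to the mean acts indirectly, through their correlation with severity.

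The waitlist data added are also not a randomised set, since these participants begin treatment only if they still want it after the wait. At stake is a statement about which patients should be offered the intensive format, drawn from data that cannot support it. The primary between-group comparison is not affected.

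**Working it through.** **The plan's own figure.** The article gives no calculation for the predictor analysis. Its only one is for the group comparison. A two-sample t-test with d = 0.92, two-sided alpha 0.05 and power 0.80 needs 19.55, so 20 per group, and adding 5 gives 25 per group and 50 in total. This reproduces, but it says nothing about predictors.

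**Inputs.** Retest reliability of SIAS and SPS is 0.91–0.93 (Primary outcome measures). Total N is 50, or 40 after the planned attrition allowance of 5 per group (Sample size calculations). The benefit is set at 0.92 SD and is identical for every participant, so there is no true moderation. Assumed: normal scores, equal variances before and after, and change regressed on baseline. Values of r below 0.91 are assumptions, shown only as a range.

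**Treated participants only.** With pre-post correlation r, the slope of change on baseline is −(1 − r), and the correlation of baseline with change is −√((1 − r)/2).

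- r = 0.93: −√(0.07/2) = −0.187
- r = 0.91: −√(0.09/2) = −0.212

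Check by Fisher z at r = 0.92, n = 50: the correlation is −√(0.08/2) = −0.20; atanh(0.20) × √47 = 1.39; Φ(1.39 − 1.96) ≈ 0.285.

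**Simulation**, 6,000 trials per setting, showing the share significant at 0.05 with no true moderation:

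| r | Correlation | Treated only, n = 50 | Treated only, n = 40 | Randomised interaction, N = 50 |
|---|---|---|---|---|
| 0.93 | −0.187 | 25.5% | 21.2% | 4.7% |
| 0.91 | −0.212 | 30.8% | 26.8% | 5.1% |
| 0.8 (assumed) | −0.316 | 62.9% | 52.4% | 5.0% |
| 0.7 (assumed) | −0.387 | 80.7% | 70.3% | 4.9% |
| 0.6 (assumed) | −0.447 | 91.2% | 83.8% | 5.1% |

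The group-by-baseline interaction averages zero and holds its 5% level at every r, because regression to the mean is the same in both randomised arms.

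**Direction depends on the form of the model.** Under the same assumptions the slope of the post-treatment score on baseline is r, that is 0.91 to 0.93. One model says that severe cases improve more and the other that they end worse. Neither measures a difference in treatment effect.

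**Precision of the interaction.** For a standardised continuous predictor, the minimum detectable interaction at 80% power is (1.96 + 0.84) × 2 × √(1 − r²)/√N.

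- N = 50, r = 0.93: 0.29 outcome SD per predictor SD
- N = 50, r = 0.91: 0.33
- N = 50, r = 0.7 (assumed): 0.57

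For an evenly split binary predictor with unadjusted outcome, the standard error is 4/√50 = 0.566. Power is Φ(0.46/0.566 − 1.96) = 13% for a 0.46 SD difference in effect, and Φ(0.92/0.566 − 1.96) = 37% for 0.92 SD.

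**The case against.** The strongest reply is that much of this concerns a model the article does not write down. It does not say that only treated participants are pooled, that change is regressed on baseline, or that waiting-period data are left out. Those data are collected at T1 to T3, and an unseen analysis plan may contain a moderator model. If the intended analysis is post-treatment score given pre-treatment score, it is a legitimate prognostic analysis and only its wording is at issue. The Background also wants predictors of adherence, which waiting controls cannot have, so a treated-participant analysis is needed for that part. The authors call the work exploratory and claim little for it, and an interaction in 50 people has low power.

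All of that stands, and it rules out three stronger readings that a reader might infer:

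- That a spurious severity finding is more likely than not. Rates of 80% and above need r of 0.7 or lower, which the document does not give. At its own 0.91–0.93, most trials would show no such finding.
- That the entry cut-offs create the problem. Eligibility requires "elevated scores on both the Social Interaction Anxiety Scale" and on the SPS at screening, but both scales are measured again at T1. This reduces regression in the mean. The baseline-change correlation comes from imperfect retest correlation, with or without selection.
- That the aim goes wholly unanswered. The article promises only initial insight.

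What the reply does not remove is the article's commitment to put uncontrolled outcomes into an analysis whose aim is worded as effectiveness and suitability. The exploratory label warns of imprecision and multiplicity. It does not change what is estimated.

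**Conclusion.** The concern holds as a mismatch between the stated aim and the data chosen to address it. The inclusion of waitlist participants' outcomes after treatment is explicit, and those outcomes can support prognostic statements only. By the protocol's own reasoning, the waitlist is what guards against regression to the mean, and that guard is absent for these outcomes.

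The size is moderate. For baseline SIAS/SPS severity the false-positive rate is about 26–31% with 50 treated and 21–27% with 40, against 5%. This is conditional on a change-on-baseline model, equal variances and r of 0.91–0.93. It would be higher if stability over the treatment interval is lower than the retest figure, which is an assumption. These rates do not carry over to age and gender. The point should be corrected before predictor results are reported, and it has no bearing on the primary comparison.

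**What to change.** 1. Add exploratory group-by-predictor interactions on the T2 score in the randomised comparison, adjusted for the T0 score. T0 precedes randomisation, whereas T1 follows it and is timed differently in the two arms. The personality measures exist only from T1, so use T1 for those and state the caveat.
2. Report each interaction with its confidence interval, and say that 50 participants can detect only large moderation, so a null result is not evidence of a uniform effect.
3. Keep the pooled analysis of treated participants for outcome and adherence. Model the post-treatment score given the pre-treatment score, label it prognostic, and do not interpret it as effectiveness or suitability.
4. Add the uncontrolled nature of that analysis to the limitations.

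The cost is a few model terms and some rewording. Trial status says that data collection is finished and analysis is under way, and Table 2 shows that the scores needed were scheduled in both arms. No new data are required. The added analysis should be dated and marked as specified after data collection.

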### Clinician support

Scheduled check-in calls will follow a standardised script. Questions are designed to prompt discussion with the participant around their understanding of the content and skills covered in the preceding modules, their goals, practice of the skills, and assistance troubleshooting any barriers or challenges to skills practice (e.g. tailoring an exposure hierarchy to their personal goals). Participants can request to complete their check-in calls via email if they are unable to speak over the phone (e.g. phone calls are too anxiety-provoking) or require less intensive support. If participants require further support over the following days, they can request a check-in call on day 5 of the program. Participants are informed that they may email the research team at any time during the treatment week with questions or if they require technical or clinical assistance (and will be responded to within business hours). All contact hours with participants will be recorded by clinicians in the REDCap platform.

### Randomisation and allocation procedures

At the completion of the telephone recruitment interview, participants will be randomised to either the iCBT for SAD group or WLC group using a 1:1 allocation ratio. Allocation numbers will be determined by a person who is completely independent of the research team, using the random.org random number generator and stored in opaque sealed envelopes, only opened by the study clinician once an offer of participation is made.

### Blinding

Treatment group allocation will be concealed from the research team and applicant until it is determined an applicant meets inclusion criteria and is invited to participate in the study. Treatment group allocation cannot be concealed from the participants or the researchers during group allocation, as participants will be informed by the researchers when they can commence their treatment. Primary outcome data will be based on self-report assessment to protect from experimenter bias. It is not feasible to conduct blinded diagnostic interviews at follow-up due to funding constraints.

### Trial outcomes and description of materials

After randomisation, all participants will complete a set of self-report questionnaires at baseline (T1), post-treatment (T2), and at 1-month follow-up (T3). Both groups will also be asked to complete a brief phone diagnostic interview [the ADIS MDD and SAD modules; [56]] at the 1-month follow-up (T3). Table 2 includes a list of assessment measures used and at which time point.

**Table 2 Tab2:** Materials used at each study time point

Questionnaire	Recruitment (T0)	Baseline (T1)	Post-treatment (T2)	One-month follow-up (T3)
Demographics	X			
Eligibility questions	X			
ADIS-5 modules	X			X
SPS	X	X	X	X
SIAS	X	X	X	X
PHQ-9	X	X	X	X
WSAS	X	X	X	X
LPFS-BF 2.0		X		X
PID-5-BF		X		X
HSU	X			
CEQ		X		
TSQ^a^			X	
Strategy use			X	X

^a^TSQ is completed by the treatment group only

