**Fig. 1 Fig1:**
[figure not shown]
Consolidated Standards of Reporting Trials (CONSORT) participant flowchart illustrating enrolment and study procedure

Applicants are next directed to complete an online screening and eligibility questionnaire, including demographic information, GP details, eligibility questions, and the SIAS, SPS, and PHQ-9. Ineligible applicants will be redirected on-screen and by email to further support services including digital mental health treatment options (e.g. the standard-paced version of the treatment through THIS WAY UP under supervision of their GP) and crisis support lines, and encouraged to speak with their GP about alterative support.

Eligible applicants will proceed to a phone call with one of the study clinicians (either a provisional psychologist, registered psychologist, or clinical psychologist) to complete additional eligibility questions, an abbreviated version of the Anxiety Disorders Interview Schedule for DSM-5 [ADIS; [56]] Social Anxiety Disorder and Major Depressive Disorder modules, and a comprehensive risk assessment.

Participants who meet inclusion criteria will be randomly allocated to one of two treatment groups (see randomisation and allocation procedures below) and verbally informed of their treatment group allocation and next steps. Participants’ general practitioners will be informed by letter of their participation and an outline of the intervention content.

Participants can self-withdraw their consent to take part in the study at any time by emailing the research team or submitting the UNSW standard withdrawal form, appended to the PISCF. Participants may also be withdrawn from the study if they experience a serious adverse event that is either attributable to the study intervention or procedure or that means they can no longer participate in the study.

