### Intervention: 7-day iCBT for social anxiety disorder group

The intervention program follows the THIS WAY UP iCBT program for social anxiety (available on www.thiswayup.org.au), using the intensive 1-week format introduced in the pilot trial [33] and described further in Table 1. Participants allocated to the intervention group (iCBT for SAD group) will be able to choose their preferred start date for the intervention as early as the week after the phone interview. To streamline tracking of participants and shared clinical care between research clinicians during business hours, participants are scheduled to begin their treatment on a Monday and end the following Sunday. A preparation call following a standardised script will be scheduled for the week prior to a participant’s treatment week, reiterating treatment week instructions, discussing their treatment goals, scheduling check-in calls for days 1 and 3, and answering any questions prior to commencement.

On the first day of the treatment week, participants will receive an automated email from the REDCap platform notifying them that their first module is available, with a written record of instructions for the coming week. Participants will complete baseline questionnaires prior to the first module. Each day participants are instructed to spend 20–30 min reading module content, before downloading a brief summary and activity plan, and spending 3–4 h over the remaining day practising the assigned skills.

Following treatment completion, participants will receive an automated email via REDCap with a link to complete post-treatment (T2) and follow-up (T3) questionnaires. At 6 weeks (T3), participants will complete the telephone diagnostic interview (SAD and MDD modules).

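### The stated baseline (T1) is self-reported after allocation is known, and under different conditions in each arm. Changes from T1 are therefore exposed, and the T2 comparison as described leaves the pre-randomisation T0 scores unused.

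*Protocol article*

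**What the plan says.** All references are to the protocol article.

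- **Randomisation.** The section Randomisation and allocation procedures fixes the moment: "At the completion of the telephone recruitment interview, participants will be randomised to either the iCBT for SAD group or WLC group". Trial recruitment processes adds that participants are then "verbally informed of their treatment group allocation and next steps".
- **Baseline.** The section Trial outcomes and description of materials puts T1 later than allocation: "After randomisation, all participants will complete a set of self-report questionnaires at baseline (T1), post-treatment (T2), and at 1-month follow-up (T3").
- **iCBT arm.** Under the Intervention heading, participants may "choose their preferred start date for the intervention as early as the week after the phone interview". Before that, "A preparation call following a standardised script will be scheduled for the week prior to" the treatment week; among other things, the call covers treatment goals. Then "Participants will complete baseline questionnaires prior to the first module".
- **Waitlist arm.** Under the Control heading, the T1 link is sent the day after the interview. The preparation call comes only before these participants' own treatment week, after T3.
- **Pre-randomisation scores.** Table 2 has a column headed "Recruitment (T0") with SPS, SIAS, PHQ-9 and WSAS marked. The use described for the first three is eligibility screening.
- **Analysis.** Statistical analysis plans random-intercept linear mixed models, pre/post contrasts and, between arms, "planned pairwise comparisons will be used to compare between-groups at post-treatment and follow-up". No baseline score is named as a covariate. The only covariate named for the outcome models is the time from intake interview to baseline, entered if a t-test shows that the arms differ on it.

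**The concern.** A baseline should be a measurement that allocation cannot have touched. Here T1 is a self-report by people who know their arm. One arm answers soon after learning that it must wait. The other answers on the point of starting treatment, after a clinician call and a longer interval. A T1 difference between arms could come from expectation, disappointment, contact with the clinician, or simply more time for scores selected on screening cut-offs to drift back. The documents give neither the size nor the direction of such a shift.

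Two things are at stake. First, any quantity that measures change from T1 or conditions on T1 can absorb the shift. Second, the comparison that does not rely on T1 gives up the precision and the correction of chance imbalance that a valid T0 covariate would bring in a trial of 50.

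**Working it through.** **1. The plan's own figure.** Sample size calculations gives d = 0.92, alpha 0.05 and power 0.80, hence 20 per arm. A two-sided, two-sample t-test gives 19.55, so 20. The figure reproduces and rests on an unadjusted comparison.

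**2. What a T1 shift does to each estimate.** Suppose knowledge of allocation and the preparation call move T1 by s SD in the iCBT arm only, and let r be the correlation between occasions.

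- Between-group difference at T2, complete data: bias 0.
- Group-by-time contrast (T2 − T1): bias of size s.
- T2 adjusted for T1: bias of size r × s.
- T2 adjusted for T0: bias 0.

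A simulation checked this with 25 per arm, complete data, r = 0.7, a true T2 difference of −0.92, an assumed T1 shift of −0.30 and 150 runs:

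| Estimate of the T2 effect | Expected | Mean | SD over runs |
|---|---|---|---|
| Raw T2 difference | −0.92 | −0.88 | 0.29 |
| Mixed-model T2 contrast (T1 as a response) | −0.92 | −0.88 | 0.29 |
| Group-by-time contrast | −0.92 + 0.30 = −0.62 | −0.63 | 0.21 |
| Adjusted for T1 | −0.92 + 0.7 × 0.30 = −0.71 | −0.70 | 0.20 |
| Adjusted for T0 | −0.92 | −0.90 | 0.20 |

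The Monte Carlo standard error of the first mean is 0.29/√150 = 0.024, so −0.88 is compatible with −0.92. The mixed-model T2 contrast equalled the raw T2 difference to about 1e−15. Carrying T1 as a response therefore neither biases that contrast nor adjusts it for baseline.

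**3. Precision available from T0.** The SE relative to the unadjusted T2 comparison is √(1 − r²), where r is now the T0–T2 correlation. The documents do not give r, so a range is assumed. Power uses the noncentral t with noncentrality (0.92/√(1 − r²)) × √(n/2), df = 2n − 3 (2n − 2 unadjusted), and two-sided alpha 0.025, the level that Statistical analysis sets for each co-primary outcome.

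| r | SE ratio | Power, 20 per arm | Power, 25 per arm |
|---|---|---|---|
| unadjusted | 1.00 | 0.72 | 0.82 |
| 0.3 | 0.95 | 0.76 | 0.86 |
| 0.4 | 0.92 | 0.795 | 0.89 |
| 0.5 | 0.87 | 0.84 | 0.92 |
| 0.6 | 0.80 | 0.90 | 0.96 |
| 0.7 | 0.71 | 0.95–0.96 (0.9546) | 0.99 |

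**4. The elapsed-time covariate.** The timing rules differ by arm, so interview-to-baseline time is largely set by arm. Assumed waits were 1–3 days for the waitlist and, for iCBT, 3 days up to a maximum of between 7 and 28 days. Arm then explains about 64% of the covariate's variance. The variance inflation is about 2.8 (1/(1 − 0.64) = 2.78), and the SE of the arm effect grows about √2.8 ≈ 1.7-fold, unless the covariate itself explains outcome variance. Being measured after randomisation, it also cannot remove an effect of knowing the allocation.

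**The case against.** The strongest reply is that the primary comparison is unharmed. The primary time point is T2, the named between-group comparison is at T2 and T3, and with complete data a shifted T1 does not enter it. That stands. A reader might infer that the trial's headline effect is biased by the full T1 shift, but the text does not support this. One-for-one bias belongs to a difference in change, which the article does not name as its between-group test. Nor can one contrast be both unadjusted for T1 and biased by it.

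Four further replies have weight:

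- Leaving out a baseline covariate costs efficiency, not validity, and covariate lists may sit in a fuller plan that is not shown.
- Any shift size is assumed. The scales address typical fear, and the article cites test–retest reliability of 0.91–0.93 for them.
- T0 was subject to eligibility cut-offs, which may lower its correlation with T2. It is therefore too strong to say that adjustment restores 80% power: at r = 0.3 and 20 per arm, power is 0.76.
- The article foresaw unequal waiting and planned a covariate for it. It did, but that device does not work, for the reasons in step 4 of the working.

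It would also be too strong to say that waitlist participants answer T1 the next day, since only the sending of the link is fixed. The same holds for saying that the iCBT arm loses more people before T1. Its window is longer, but no figures are given.

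**Conclusion.** The point holds in a limited form. T1 follows randomisation and disclosure in both arms, and follows a preparation call and a longer wait in one. Pre/post contrasts, within-group g, any group-by-time or T1-adjusted test, and missing-data handling that relies on T1 are exposed to a shift that the documents do not let anyone size or sign. The T2 pairwise comparison remains valid with complete data but, as described, has no baseline adjustment.

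The gain forgone depends on the assumed T0–T2 correlation of 0.3–0.7: an SE lower by about 5–29%, and power up from 0.72 to 0.76–0.96 at 20 per arm, or from 0.82 to 0.86–0.99 at 25. Range restriction on T0 points to the lower end. These power figures take d = 0.92 as given. Severity: should fix. With data collection finished and analysis under way, a demand to replace the primary model unconditionally would go too far.

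**What to change.** - Estimate the T2 and T3 between-group differences with the participant's T0 score on the same scale as covariate. Alternatively, fit a constrained-baseline model in which T0 is the common pre-randomisation mean. Only the second formally retains randomised people with no later data; with T0 purely as a covariate, someone without T2 and T3 still drops out.
- Do not adjust for T1, since that would import part of any shift.
- Drop the elapsed-time covariate that is triggered by a t-test.
- Report change from T1 and within-group g as descriptive.
- If results have already been seen, say so, label the T0-adjusted analysis accordingly, and report it beside the planned one.

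The cost is some wording and one model respecification with data already collected. One limit remains: T2 is counted from T1, so it falls later after randomisation in the iCBT arm. T0 adjustment does not equalise that interval, and the report should state it.
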